### 8.1.4 Serious Adverse Event or Serious Adverse Reaction

A serious adverse event or reaction is any untoward medical occurrence that at any dose:

- Results in death,
- Is life-threatening,

NOTE: The term "life-threatening" in the definition of "serious" refers to an event in which the participant was at risk of death at the time of the event; it does not refer to an event which hypothetically might have caused death if it were more severe.

- Requires inpatient hospitalisation or prolongation of existing hospitalisation,
- Results in persistent or significant disability/incapacity, or
- Is a congenital anomaly/birth defect.
- Other important medical events*

*Other events that may not result in death, are not life threatening, or do not require hospitalisation, may be considered a serious adverse event when, based upon appropriate medical judgement, the event may jeopardise the patient andmay require medical or surgical intervention to prevent one of the outcomes listed above.

### 8.1.5 Expected Serious Adverse Events/Reactions

No serious adverse events are expected from the vaccines administered in this study. All vaccines used are already licensed and used in several European countries.

### 8.1.6 Suspected Unexpected Serious Adverse Reactions

A serious adverse reaction, the nature or severity of which is not consistent with the summary of product characteristics.

### 8.1.7 Medically Significant adverse events

An adverse event that results in a consultation with a physician or other health professional

## 8.2 Reporting Procedures for All Adverse Events

All AEs attributed to the administration of DTaP-IPV-Hib, MenC-CRM197, MenC-TT, PCV13 and Hib-MenC observed by the investigator or reported by the participant, will be recorded on the CRF. All solicited and unsolicited adverse events will be recorded for 4 days following immunisation on diary cards. Unsolicited medically significant adverse events occurring between visit 1 and 4 will be recorded on diary cards, as will those occurring between visit 5 and 7.

The following information will be recorded: description, date of onset and end date, severity, assessment of relatedness to study medication, other suspect drug or device and action taken. The relationship of AEs to the study medication will be assessed by a medically qualified investigator.

All SAEs will be recorded through the whole study. Follow-up information should be provided as necessary.

These AEs considered to be related to the study medication as judged by a medically qualified investigator or the sponsor will be followed until resolution or the event is considered stable. All related AEs that result in a participant’s withdrawal from the study or are present at the end of the study, should be followed up until a satisfactory resolution occurs.

It will be left to the investigator’s clinical judgment whether or not an AE is of sufficient severity to require the participant’s removal from the study (see section 6.6). A participant may also be voluntarily withdrawn from the study by a parent/guardian due to what he or she perceives as an intolerable AE. If either of these occurs, the participant must undergo an end of study assessment and be given appropriate care under medical supervision until symptoms cease or the condition becomes stable.

## Reporting Procedures for Serious Adverse Events

The Oxford Radcliffe Hospitals Trust / University of Oxford Trials Safety Group (TSG) will undertake to review immediately reported SAEs for the study.  They will meet at regular intervals and consider:

- Occurrence and nature of adverse events
- Whether additional information on adverse events is required
- Consider taking appropriate action where necessary to halt trials
- Act / advise on incidents occurring between meetings that require rapid assessment (eg SUSARs)

All SAEs (from all sites) must be reported to the University of Oxford CTRG within one working day of discovery or notification of the event. CTRG will perform an initial check of the information and ensure that it is reviewed at the next TSG meeting. All SAE information must be recorded on an SAE form and faxed to CTRG. Additional information received for a case (follow-up or corrections to the original case) need to be detailed on a new SAE form and faxed to CTRG.

The CI will report all SUSARs to the Competent Authorities (MHRA in the UK and MA in Malta) and the Research Ethics Committee concerned. SUSARs occurring in the UK will only be reported to the MHRA, whereas SUSARs occurring in Malta will be reported to the MHRA and the MA. All SUSARs reported to the MHRA and MA will be reported to EudraVigilance. Fatal or life-threatening SUSARs must be reported within 7 days and all other SUSARs within 15 days. The CI will also inform all investigators concerned of relevant information about SUSARs that could adversely affect the safety of participants. The CI will also report SAEs that are considered related to the administration of study vaccines, or to study procedures, in an annual safety report to the Competent Authorities (MHRA in the UK and MA in Malta) and the Research Ethics Committee concerned. All safety reports to the MHRA must be made electronically from the 1st of September 2010.

In addition to the expedited reporting above, the CI shall submit once a year throughout the clinical trial or on request a safety report to the Competent Authority (MHRA in the UK and MA in Malta) and Ethics Committee.

# STATISTICS

## Endpoint analysis will be carried out after all participants have completed visit 7 (13 month blood sample). An additional analysis will be carried out after the final follow-up visit at 24 months of age (visit 8). An interim analysis will be carried out after all participants have completed visit 4 (5 month blood sample).

## 9.1 Description of Statistical Methods

**A)** ***Description of demographics***

Baseline demographic characteristics (age in weeks, gender, race) of each study dose group will be tabulated.

The number of subjects, mean age (plus range and standard deviation) by gender of the enrolled subjects, as a whole, and per study dose group, will be reported.

The trial completion rate will be reported, together with the time and number of withdrawals and the reason for withdrawal, for each study dose group.

**B)** ***Analysis of Immunogenicity***

***Descriptive analysis:***

Summary statistics will be calculated for the following outcomes assessed at 1 month after completion of the primary immunisation, at 12 months plus 6 days and at 12 months plus 28 days and 24 months after the Hib-MenC booster dose for each study dose group. Continuous variables will be reported as means and standard deviations, and categorical variables will be reported as counts and percentages, together with the numbers of observations in all cases.

- MenC rSBA GMT
- Number of MenC specific memory B cells in the blood
- *S. pneumoniae* IgG GMC response for each of the 13 serotypes
- Pneumococcal serotype specific B cell phenotype
- Anti-PRP IgG GMC response
- Anti-tetanus toxoid GMC response
- Percentages of subjects with MenC rSBA ≥1:8 and ≥ 1:128
- Percentages of subjects with MenC rSBA GMT ≥ 1000
- Percentages of subjects with *S. pneumoniae* IgG ≥ 0.35 μg/ml for each of the 13 serotypes
- Percentages of subjects with anti-PRP IgG ≥0.15 μg/ml and ≥ 1.0 μg/ml
- Percentages of subjects with anti-tetanus toxoid > 0.1 IU/ml

***Statistical Analysis***

The analysis of the outcome variables will be performed on the intention–to-treat (ITT) population for the reduced dose MenC objectives and the completers population for the alternating limb objectives. A subject is included in the ITT population if they have at least one dose and at least one post-baseline assessment, and in the completers population if they receive all doses of vaccine and have all planned assessments.

An analysis of variance will be performed when the outcome variable is continuous. The model will contain the terms dose group (4 levels) and alternating limb group (2 levels). A term for centre will be included in the model. The results of a comparison between any two levels of a factor will be reported as a treatment effect with 95% confidence interval.

For the analysis of variables relating only to 0 dose control group the term relating to dose group will be omitted.

The following outcomes will be analysed (comparisons of interest are listed):

1. MenC rSBA GMT response variable assessed 28 days after the Hib-MenC 12 month booster dose
   1. Single dose MenC-CRM197 Group vs. Two dose MenC Group
   2. Single dose MenC-CRM197 Group vs. 0 dose control Group
   3. Single dose MenC-TT Group vs 0 dose control Group
   4. Two dose MenC Group vs. 0 dose control Group
   5. Single Dose MenC-CRM197 Group vs Single Dose MenC-TT Group
2. MenC rSBA GMT response variable assessed 6 days after the Hib-MenC 12 month booster dose
   1. Single dose MenC-CRM197 Group vs. Two dose MenC Group
   2. Single dose MenC-CRM197 Group vs. 0 dose control Group
   3. Single dose MenC-TT Group vs 0 dose control Group
   4. Two dose MenC Group vs. 0 dose control Group
   5. Single dose MenC-CRM197 Group vs Single dose MenC-TT Group

3. MenC rSBA GMT response variable assessed 12 months after the Hib-MenC 12 month booster dose

1. Single dose MenC-CRM197 Group vs. Two dose MenC Group
2. Single dose MenC-CRM197 Group vs. 0 dose control Group
3. Single dose MenC-TT Group vs 0 dose control Group
4. Two dose MenC Group vs. 0 dose control Group
5. Single dose MenC-CRM197 Group vs Single dose MenC-TT Group
6. MenC rSBA GMT response variable (persistence) assessed at 12 months of age
   1. Single dose MenC-CRM197 Group vs. Two dose MenC Group
   2. Single dose MenC-CRM197 Group vs. 0 dose control Group
   3. Single dose MenC-TT Group vs 0 dose control Group
   4. Two dose MenC Group vs. 0 dose control Group
   5. Single dose MenC-CRM197 Group vs Single dose MenC-TT Group
7. MenC rSBA GMT response variable assessed at 5 months of age
   1. Single dose MenC-CRM197 Group vs. Two dose MenC Group
   2. Single dose MenC-CRM197 Group vs. 0 dose control Group
   3. Single dose MenC-TT Group vs 0 dose control Group
   4. Two dose MenC Group vs. 0 dose control Group
   5. Single dose MenC-CRM197 Group vs Single dose MenC-TT Group
8. the numbers of MenC specific memory B cells in the blood at 5 months of age
   1. Single dose MenC-CRM197 Group vs. Two dose MenC Group
   2. Single Dose MenC-CRM197 Group vs Single Dose MenC-TT Group
9. the numbers of MenC specific memory B cells in the blood at 12 months of age
   1. Single dose MenC-CRM197 Group vs. Two dose MenC Group
   2. Single dose MenC-CRM197 Group vs. 0 dose control Group
   3. Single dose MenC-TT Group vs 0 dose control Group
   4. Two dose MenC Group vs. 0 dose control Group
   5. Single dose MenC-CRM197 Group vs Single dose MenC-TT Group
10. the numbers of MenC specific memory B cells in the blood at 6 days after the Hib-MenC 12 month booster dose
    1. Single dose MenC-CRM197 Group vs. Two dose MenC Group
    2. Single dose MenC-CRM197 Group vs. 0 dose control Group
    3. Single dose MenC-TT Group vs 0 dose control Group
    4. Two dose MenC Group vs. 0 dose control Group
    5. Single dose MenC-CRM197 Group vs Single dose MenC-TT Group
11. The numbers of specific memory B cells in the blood at 28 days after the Hib-MenC 12 month booster dose
    1. Single dose MenC-CRM197 Group vs. Two dose MenC Group
    2. Single dose MenC-CRM197 Group vs. 0 dose control Group
    3. Single dose MenC-TT Group vs 0 dose control Group
    4. Two dose MenC Group vs. 0 dose control Group
    5. Single dose MenC-CRM197 Group vs Single dose MenC-TT Group
12. The numbers of specific memory B cells in the blood at 11-12 months after the Hib-MenC booster dose
    1. Single dose MenC-CRM197 Group vs. Two dose MenC Group
    2. Single dose MenC-CRM197 Group vs. 0 dose control Group
    3. Single dose MenC-TT Group vs 0 dose control Group
    4. Two dose MenC Group vs. 0 dose control Group
    5. Single dose MenC-CRM197 Group vs Single dose MenC-TT Group
13. The *S. pneumoniae* IgG GMC response variable for each of the thirteen serotypes separately at 5 months of age
    1. the consistent limb group vs. the alternating limb group
14. the *S. pneumoniae* IgG GMC response variable for each of the thirteen serotypes separately, (persistence) at 12 months of age
    1. the consistent limb group vs. the alternating limb group

1. the *S. pneumoniae* IgG GMC response variable for each of the thirteen serotypes separately at 13 months of age after the PCV-13 booster dose
   1. the consistent limb group vs. the alternating limb group
2. 12. the *S. pneumoniae* IgG GMC response variable for each of the 13 serotypes separately at 24 months of age.
   1. the consistent limb group vs. the alternating limb group

1. the anti-PRP IgG GMC response variable at 5 months of age
   1. the consistent limb group vs. the alternating limb group
2. the anti-PRP IgG GMC response variable (persistence) at 12 months of age
   1. the consistent limb group vs. the alternating limb group

1. the anti-PRP IgG GMC response variable at 13 months of age, after the Hib-MenC booster dose
   1. the consistent limb group vs. the alternating limb group
2. the anti-PRP IgG GMC response variable at 24 months of age
   1. the consistent limb group vs. the alternating limb group
3. the anti-tetanus toxoid GMC response variable at 5 months of age ,
   1. the consistent limb group vs. the alternating limb group
4. the anti-tetanus toxoid GMC response variable (persistence) at 12 months of age
   1. the consistent limb group vs. the alternating limb group

1. the anti-tetanus toxoid GMC response variable at 13 months of age
   1. the consistent limb group vs. the alternating limb group
2. the anti-tetanus toxoid GMC response variable at 24 months of age
   1. the consistent limb group vs. the alternating limb group

The binary variables will be analysed using logistic regression. The model will contain the terms dose group (4 levels), and alternating limb group (2 levels). There will also be a term for centre. The results of a comparison between two levels of a factor will be reported as an odds ratio and as a risk difference, with 95% confidence intervals.

For the analysis of variables relating only to 0 dose control group the term for dose group will be omitted.

The following binary outcomes will be analysed:

1. percentage of infants with MenC rSBA ≥ 1:8 and ≥ 1:128 assessed 6 days after the 12 month Hib-MenC booster
   1. Single dose MenC-CRM197 Group vs. Two dose MenC Group
   2. Single dose MenC-CRM197 Group vs. 0 dose control Group
   3. Single dose MenC-TT Group vs 0 dose control Group
   4. Two dose MenC Group vs. 0 dose control Group
   5. Single dose MenC-CRM197 Group vs Single dose MenC-TT Group

1. percentage of infants with MenC rSBA ≥ 1:8 and ≥ 1:128 assessed 28 days after the 12 month Hib-MenC booster
   1. Single dose MenC-CRM197 Group vs. Two dose MenC Group
   2. Single dose MenC-CRM197 Group vs. 0 dose control Group
   3. Single dose MenC-TT Group vs 0 dose control Group
   4. Two dose MenC Group vs. 0 dose control Group
   5. Single dose MenC-CRM197 Group vs Single dose MenC-TT Group

1. percentage of infants with MenC rSBA ≥ 1:8 and ≥1:128 assessed at 12 months of age
   1. Single dose MenC-CRM197 Group vs. Two dose MenC Group
   2. Single dose MenC-CRM197 Group vs. 0 dose control Group
   3. Single dose MenC-TT Group vs 0 dose control Group
   4. Two dose MenC Group vs. 0 dose control Group
   5. Single dose MenC-CRM197 Group vs Single dose MenC-TT Group
2. percentage of infants with MenC rSBA ≥ 1:8 and ≥1:128 at 5 months of age
   1. Single dose MenC-CRM197 Group vs. Two dose MenC Group
   2. Single dose MenC-CRM197 Group vs. 0 dose control Group
   3. Single dose MenC-TT Group vs 0 dose control Group
   4. Two dose MenC Group vs. 0 dose control Group
   5. Single dose MenC-CRM197 Group vs Single dose MenC-TT Group
3. percentage of infants with MenC rSBA ≥ 1:8 and ≥1:128 at 24 months of age
   1. Single dose MenC-CRM197 Group vs. Two dose MenC Group
   2. Single dose MenC-CRM197 Group vs. 0 dose control Group
   3. Single dose MenC-TT Group vs 0 dose control Group
   4. Two dose MenC Group vs. 0 dose control Group
   5. Single dose MenC-CRM197 Group vs Single dose MenC-TT Group
4. percentage of infants with MenC rSBA GMT ≥ 1000 assessed 6 days after the 12 month Hib-MenC booster
   1. Single dose MenC-CRM197 Group vs. Two dose MenC Group
   2. Single dose MenC-CRM197 Group vs. 0 dose control Group
   3. Single dose MenC-TT Group vs 0 dose control Group
   4. Two dose MenC Group vs. 0 dose control Group
   5. Single dose MenC-CRM197 Group vs Single dose MenC-TT Group
5. percentage of infants with MenC rSBA GMT ≥ 1000 assessed 28 days after the 12 month Hib-MenC booster
   1. Single dose MenC-CRM197 Group vs. Two dose MenC Group
   2. Single dose MenC-CRM197 Group vs. 0 dose control Group
   3. Single dose MenC-TT Group vs 0 dose control Group
   4. Two dose MenC Group vs. 0 dose control Group
   5. Single dose MenC-CRM197 Group vs Single dose MenC-TT Group

1. percentage of infants with *S. pneumoniae* IgG ≥ 0.35 μg/ml for each of the 13 serotypes at 5 months of age
2. the consistent limb group vs. the alternating limb group
3. percentage of infants with *S. pneumoniae* IgG ≥ 0.35 μg/ml for each of the 13 serotypes at 12 months of age
4. the consistent limb group vs. the alternating limb group
5. percentage of infants with *S. pneumoniae* IgG ≥ 0.35 μg/ml for each of the 13 serotypes at 13 months of age after the PCV-13 booster dose
6. the consistent limb group vs. the alternating limb group
7. percentage of infants with *S. pneumoniae* IgG ≥ 0.35 μg/ml for each of the 13 serotypes at 24 months of age after the PCV-13 booster dose
   1. the consistent limb group vs. the alternating limb group
8. percentage of infants with anti-PRP IgG ≥ 0.15 μg/ml and ≥ 1.0 μg/ml at 5 months of age
9. the consistent limb group vs. the alternating limb group
10. percentage of infants with anti- PRP IgG ≥ 0.15 μg/ml and ≥ 1.0 μg/ml at 12 months of age
11. the consistent limb group vs. the alternating limb group
12. percentage of infants with anti-PRP IgG ≥ 0.15 μg/ml and ≥ 1.0 μg/ml at 13 months of age, after the Hib-MenC booster dose
    1. the consistent limb group vs. the alternating limb group
13. percentage of infants with anti-PRP IgG ≥ 0.15 μg/ml and ≥ 1.0 μg/ml at 24 months of age
    1. the consistent limb group vs. the alternating limb group
14. percentage of infants with anti- tetanus toxoid >0.1 IU/ml at 5 months of age
15. the consistent limb group vs. the alternating limb group
16. percentage of infants with anti- tetanus toxoid >0.1 IU/ml at 12 months of age
17. the consistent limb group vs. the alternating limb group
18. percentage of infants with anti- tetanus toxoid >0.1 lU/ml at 13 months of age
    1. the consistent limb group vs. the alternating limb group
19. percentage of infants with anti- tetanus toxoid >0.1 lU/ml at 24 months of age
    1. the consistent limb group vs. the alternating limb group

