7. It is intended to measure the numbers of MenC specific memory B cells in the blood at 5 months, 12 months, 6 days following the 12 month booster dose, at 13 months and 24 months on a subset of participants. Specific memory B cells against diphtheria and tetanus will also be measured and used as a control. As many participants as possible would be included in this subset but the number would be determined by the practicalities of getting the blood to the laboratory in time (before midday) for processing.

8. To assess the local and systemic adverse reactions experienced by participants in the four different study groups after immunisation with each dose of the MenC-CRM197, MenC-TT and Hib-MenC vaccines.

Alternating limb component

1. To compare the *S. pneumonia*e IgG GMCs and percentage of infants with serum concentration of *S. pneumonia*e specific IgG ≥0.35 g/ml for all 13 PCV13 serotypes at 5, 12, 13 and 24 months of age in children receiving PCV13 in a consistent limb (subgroups ‘a’) vs those receiving this in alternating limbs (subgroups ‘b’).
2. To compare serotype specific pneumococcal B cell phenotype in a subset of participants at 5, 12, 13 and 24 months of age in children receiving PCV13 in a consistent limb (sub groups ‘a’) vs those receiving this in alternating limbs (subgroups ‘b’).

3. To compare the anti-PRP IgG GMCs and percentage of infants with serum concentration of anti-PRP IgG ≥0.15g/ml and ≥1.0 g/ml and at 5, 12, 13 and 24 months of age in children receiving DTaP-IPV-Hib in a consistent limb (sub groups ‘a’) vs those receiving this in alternating limbs (subgroups ‘b’).

4. To compare the anti-tetanus toxoid GMCs and percentage of infants with anti-tetanus toxoid >0.1 IU/ml at 5,12, 13 and 24 months of age in children receiving DTaP-IPV-Hib in a consistent limb (sub groups ‘a’) vs those receiving this in alternating limbs (subgroups ‘b’)

5. To compare the local or systemic vaccine reactions in subgroups a and b at each vaccination time point.

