## 6.3.4 Elimination criteria during the study

The following criteria will be checked at each visit subsequent to the first visit and if any become applicable during the study, it will not require withdrawal of the participant from the study but may determine the participant’s evaluability in the completer’s population (CP) analysis, in which case the data would be included in the Intention to Treat (ITT) analysis.

- Use of any investigational or non-registered product (drug or vaccine) other than the study vaccine(s) during the study period, until 1 month after the administration of the final study vaccine (ie at 12 months of age).
- Chronic administration (defined as more than 14 days) of immunosuppressants or other immune-modifying drugs during the study period. (For corticosteroids, this will mean prednisone, or equivalent,  0.5 mg/kg/day. Inhaled and topical steroids are allowed.)
- Administration of a vaccine not foreseen by the study protocol during the period starting from 30 days before each dose of vaccine(s) and ending 30 days after.
- Administration of immunoglobulins and/or any blood products during the study period.
- Administration of any of the vaccines used in the study outside of the stipulated time period
- Administration of any of the vaccines used in the study in an incorrect limb

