## 9.7 Inclusion in Analysis

The immunogenicity analysis will be performed on both an intention to treat (ITT) population (all participants completing their designated primary and booster stage immunisation courses, and providing blood samples at the timepoint being analysed) and on a completers protocol (CP) population (all participants in the intention to treat analysis completing the study without any significant protocol deviations).

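### The main analysis set for the limb comparisons requires every planned assessment, so the 5-, 12- and 13-month results depend on later attendance, and sections 9.1 and 9.7 do not settle which limb result leads

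*Protocol*

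**What the plan says.** The limb objectives in section 5.2 are separate comparisons of randomised subgroups a and b at four ages; for pneumococcal IgG, for example, "at 5, 12, 13 and 24 months of age in children receiving PCV13 in a consistent limb" against the alternating-limb subgroup. The PRP and tetanus objectives use the same ages.

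Section 9.1 (part B, Statistical Analysis) splits the analysis sets by objective: ITT for the reduced-dose MenC objectives and "the completers population for the alternating limb objectives". An infant is placed "in the completers population if they receive all doses of vaccine and have all planned assessments". The same paragraph defines the other set: "A subject is included in the ITT population if they have at least one dose and at least one post-baseline assessment".

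Section 9.7 makes no split by objective: "The immunogenicity analysis will be performed on both an intention to treat (ITT) population" and on a completers protocol (CP) set. Its definitions also differ from those in 9.1. ITT there means "all participants completing their designated primary and booster stage immunisation courses, and providing blood samples at the timepoint being analysed"; CP means "all participants in the intention to treat analysis completing the study without any significant protocol deviations".

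Section 6.3.4 lists elimination criteria that may affect evaluability in the completers analysis, with the data then going to ITT. One of them is "Administration of any of the vaccines used in the study in an incorrect limb".

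**The concern.** A 5-month antibody comparison between two randomised subgroups needs only a 5-month result. The 9.1 definition also asks for the 12-, 13- and 24-month samples and, read literally, for the 6-day sample in the 256 infants allocated to Visit 6. No limb outcome uses the 6-day sample. The comparisons at 5, 12 and 13 months are therefore conditioned on what happens after the outcome was measured, up to 19 months later for the 5-month result. This costs precision. It also gives up part of the protection of randomisation in an open-label trial, and nothing is gained in return: these are comparisons for a difference, so there is no non-inferiority argument for a restricted set.

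Section 9.7 adds a second difficulty. It promises both sets for immunogenicity, defines completers by protocol deviations rather than by assessments, and does not say which limb result leads. Under sections 6.3.4 and 9.7 an infant could also be removed for a limb error, which is non-adherence to the very factor being compared.

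**Working it through.** **1. The plan's own figures.** The protocol gives no sample size, power or expected loss for the limb comparisons; section 9.2 calls them pilot data. Its only loss figure is 12.5%, set for the primary MenC comparison. That calculation reproduces: with SD 0.9, margin 0.35, one-sided 2.5% and 90% power, the normal formula gives 139 per group (142 with a margin of 0.347) against the stated 140, and 140/0.875 = 160. It does not bear on the limb set except as the source of the 12.5%.

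**2. Which 5-month results survive under each section.**

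| Event after a valid 5-month sample | 9.1 completers | 9.7 ITT | 9.7 CP |
|---|---|---|---|
| 24-month sample missing | out | in | out if the study is not completed |
| Visit 6 missed (allocated infant) | out, read literally | in | unclear |
| 12-month booster missed | out | out | out |
| A dose given in the wrong limb | in, on the 9.1 wording | in | may be out (6.3.4, or as a significant deviation) |

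**3. Loss if total non-completion equals the 12.5% allowance.** Completers: 498 × 0.875 = 436. The largest possible loss at 5 months arises if every non-completer had given a 5-month sample: 62/498 = 12.5%. The ratio of interval widths is √(498/436) = 1.069, so about 7% wider at most.

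**4. Loss if samples are missed independently at rate q per visit (assumed).** Four blood samples are planned for 498 − 256 = 242 infants and five for 256.

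- Infants with a 5-month sample: 498(1 − q)
- Completers: 242(1 − q)⁴ + 256(1 − q)⁵
- Ratio of interval widths: √(available / completers)

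| q | 5-month sample | Completers | 5-month results lost | Interval wider by |
|---|---|---|---|---|
| 3% | 483 | 434 | 10.1% | 5.5% |
| 5% | 473 | 395 | 16.5% | 9.4% |
| 10% | 448 | 310 | 30.8% | 20.3% |

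Under this assumption the loss is the same at 12 and 13 months. At q = 5%, dropping the Visit 6 requirement alone would raise completers to 498 × 0.95⁴ = 406, so that requirement accounts for about 10 infants.

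**5. Plausibility.** A rate of 3% implies (498 − 434)/498 = 12.9% non-completion, close to the plan's allowance; its 10.1% loss lies inside the bound in step 3. A rate of 5% implies (498 − 395)/498 = 20.7%, above the allowance. Step 3 and the 3% row are therefore nearest to what the protocol itself anticipates.

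**6. Loss by dropout only (assumed).** With 95% sampled at 5 months and 12.5% to 30% lost by 24 months, 1 − 0.875/0.95 = 8% to 1 − 0.70/0.95 = 26% of 5-month results are lost, and intervals are 4% to 16% wider.

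**The case against.** **The data are kept elsewhere.** A reader might infer from 9.1 that early results are discarded outright. The documents do not support that. Section 9.7 also runs an ITT analysis that needs a sample only at the age analysed, and section 6.6 keeps samples already collected from withdrawn infants. This stands, with a limit: the 9.7 ITT set also requires the booster course, so it still drops a 5-month result when the booster is missed. It is also possible to read 9.1 as naming the leading set and 9.7 as adding the other, but neither section says so.

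**Limb errors.** A reader might also infer that the 9.1 completers definition excludes infants vaccinated in a wrong limb. It does not mention limb. Exclusion could come only from section 6.3.4, which is worded as a possibility, or from the 9.7 CP definition if a limb error counts as a significant deviation.

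**Timing.** The opening of section 9 schedules analyses after Visit 4 and after Visit 7. Attendance at Visit 8 is not known for the cohort then, so a missing 24-month sample cannot remove anyone at those analyses. That is correct, but it shows that the 9.1 set cannot be formed as written at two of the three planned analyses.

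**Bias.** The subgroups share vaccines, visits and blood samples, so nothing in the protocol shows different attendance. Subgroup b has the more complex PCV13 pattern (left leg, right leg, left arm, against right leg throughout), so unequal limb errors are plausible. They are not demonstrated.

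**Size and purpose.** Independence of missed samples makes the loss larger than if they cluster in the same infants, and the protocol allows second venepuncture attempts and return visits. The limb question is mechanistic and pilot, so an analysis of fully vaccinated infants has a rationale. That rationale does not extend to requiring later samples.

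**Conclusion.** The concern holds in a limited form. Section 9.1 ties each limb comparison to a completers set that is not specific to an age, so the 5-, 12- and 13-month comparisons are conditioned on later attendance and, literally, on an irrelevant visit. Section 9.7 conflicts with that assignment and leaves the leading limb result open.

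The cost in precision is modest: at most 12.5% of 5-month results and an interval up to about 7% wider if total non-completion matches the plan's allowance, or about 16.5% and 9% at an assumed independent 5% missing per visit. Both rest on assumptions, because the protocol gives no rate of missing samples per visit and no loss to 24 months.

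Two further inferences are not supported. No loss of planned power can be claimed, because the component has no sample size or assumed effect. Bias between subgroups a and b cannot be asserted or sized, although selection on events after randomisation makes it possible. As the component is meant to supply pilot estimates, avoidable imprecision and selection are still worth removing.

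**What to change.** - **Section 9.1:** make the main analysis of each limb outcome at each age all randomised infants with a valid assay result at that age, analysed in the limb subgroup to which they were randomised, regardless of later missed visits or limb errors.
- **Supportive analysis:** keep a completers or per-protocol analysis, with one definition, and do not require the Visit 6 sample for it.
- **Sections 6.3.4 and 9.7:** align both with this order, and state that limb errors affect only the supportive analysis.

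The cost is a few sentences. No extra infants, samples or assays are needed, and the set can be formed at each planned analysis. The small downside is slight dilution of the biological contrast by the few infants vaccinated in a wrong limb, which the supportive analysis covers. The change does not address infants with no sample at the age in question; section 9.5 makes no allowance for them either way.
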